#### 11.5.2.6 ADVERSE EVENTS ANALYSIS

Any undesirable signs, symptoms or medical conditions occurring or worsening of pre-existing conditions between signing informed consent and the first administration study medication are considered as pre-treatment AEs. Undesirable signs, symptoms or medical conditions or worsening of pre-existing conditions occurring after the first administration of study medication are considered as treatment emergent adverse events (TEAEs).

A TEAE will be analysed as related to study medication (i.e. as adverse drug reaction, ADR) if the relationship to study treatment was documented as “unlikely”, “possible”, “probable”, or “definite” or if the relationship to study treatment is missing.

An overview table presenting the incidence of the following AE categories will be presented. Percentage of patients in each category will be compared between treatments as a difference in proportions between treatments including a 95% CI based on the (Agresti and Caffo, 2000).

All AEs

- Pre-treatment AEs
- Serious AEs (SAEs) (including pre-treatment SAEs)
- Treatment emergent SAEs (TESAEs)
- Severe TEAEs
- Related TEAEs
- Related severe TEAEs
- TEAEs leading to permanent discontinuation (i.e. withdrawal) of study medication
- Related TEAEs leading to permanent discontinuation of study medication
- AEs leading to death (i.e., outcome of AE is fatal)
- TEAEs leading to death
- Related TEAEs leading to death

All treatment emergent AEs (TEAEs) and all serious TEAEs will be tabulated by MedDRA SOC and PT presenting the number and percentage of patients reporting the AE and the number of AEs reported. Additional tables will distinguish the events by whether the AE was related to study medication and by maximum severity.

All AEs documented in the eCRF will be listed by patient. Data listings will include patient ID, treatment group, verbatim term, preferred term, system organ class, start and stop date and relative day of the AE, severity, medications (yes/no), seriousness, action taken with study medication, relationship to study medication, and outcome will be provided. TEAEs will be flagged as such. In addition, separate listings for all SAE's, deaths and AEs leading to discontinuation (action taken with study treatment = drug withdrawal or AE is reason for early termination) will be presented.

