#### 9.3.1.2 CAUSALITY ASSESSMENT

A guide for the assessment and interpretation of the causality question is provided in Appendix [Section 14.1.6.1](#).

In general causality rating against the study intervention(s) in the STROACT study will be defined as “unlikely”, “possible”, “probable”, or “definite”.

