#### 9.3.1.3 ADVERSE EVENT VARIABLES

The following variables will be collected for each AE:

- AE (verbatim).
- The date and time when the AE started and stopped.
- CTCAE grade/maximum intensity or CTCAE grade/changes in CTCAE grade/intensity.
- Whether the AE is serious or not ([Section 14.1.1](#) and [Section 14.1.2](#)).
- Investigator causality rating against the study intervention(s) (unlikely”, “possible”, “probable”, or “definite”).
- Action taken with regard to study intervention(s).
- AE caused participant’s withdrawal from study (yes or no).
- Administration of treatment for the AE.
- Outcome.

In addition, the following variables will be collected for SAEs:

- Date AE met criteria for SAE.

- Date investigator became aware of SAE.
- Seriousness criteria.
- Date of hospitalisation.
- Date of discharge.
- Probable cause of death.
- Date of death.
- Autopsy performed.
- Causality assessment in relation to study procedure(s).
- Causality assessment to other medication.

The grading scales defined in NCI CTCAE will be used for all events with an assigned CTCAE grading. For those events without assigned CTCAE grades, the recommendation in the CTCAE criteria that converts mild, moderate, and severe events into CTCAE grades should be used. (CTCAE can be assessed and/or downloaded from the Cancer Therapy Evaluation Program website <http://ctep.cancer.gov>).

---

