#### 14.1.4 ADVERSE REACTION (AR)

Adverse reaction (AR) to an investigational medicinal product is defined as all untoward and unintended responses to an investigational medicinal product related to any dose administered. All adverse events judged by either the reporting investigator or the sponsor as having a reasonable causal relationship to a medicinal product qualify as adverse reactions. The expression reasonable causal relationship means to convey in general that there is evidence or argument to suggest a causal relationship.

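### As written, the adverse-event analysis classes every treatment-emergent AE as drug-related, because all four collectable causality ratings, and a missing rating, count as related

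*Protocol*

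**What the plan says.** Three parts of the protocol bear on this.

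- **The scale.** Section 9.3.1.2 states: "In general causality rating against the study intervention(s) in the STROACT study will be defined as “unlikely”, “possible”, “probable”, or “definite". Section 9.3.1.3, which lists the variables recorded for every AE, repeats it: "Investigator causality rating against the study intervention(s) (unlikely”, “possible”, “probable”, or “definite". Neither section has a level meaning not related.
- **The analysis rule.** Section 11.5.2.6 treats a TEAE as related, and labels it an adverse drug reaction, if "the relationship to study treatment was documented as “unlikely”, “possible”, “probable”, or “definite" "or if the relationship to study treatment is missing".
- **The definition of a reaction.** Section 14.1.4 says that events judged by the investigator or sponsor "as having a reasonable causal relationship to a medicinal product qualify as adverse reactions", and explains: "The expression reasonable causal relationship means to convey in general that there is evidence or argument to suggest a causal relationship".

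Section 11.5.2.6 then plans outputs that need a split by relatedness. The overview table has four rows for related events: related TEAEs, related severe TEAEs, related TEAEs leading to permanent discontinuation, and related TEAEs leading to death. Each is to be compared between treatments with a 95% CI. The section also plans SOC and preferred-term tables: "Additional tables will distinguish the events by whether the AE was related to study medication and by maximum severity".

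**The concern.** A related/unrelated split is informative only if some events can fall on each side. Here the values an investigator can record and the values the analysis calls related appear to be the same set.

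If so, the report would describe every TEAE, including every treatment-emergent death and every event after saline, as an adverse drug reaction. The protocol describes this as the first study of the sequential therapy (2.3) and says these patients have many comorbidities (2.3.1), so a good share of events may come from the stroke or background disease. A table that attributes all of them to treatment would mislead a reader and would not do what 11.5.2.6 sets out to do.

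**Working it through.** No sample size, power or alpha figure is involved, and the protocol states no number to reproduce. The check compares two sets.

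**Step 1: values the causality variable can take** (9.3.1.2, 9.3.1.3, plus missing)

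V = {unlikely, possible, probable, definite, missing}: 5 values.

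I looked for a further level elsewhere. The causality guide lies under 14.1.6.2 (9.3.1.2 points to 14.1.6.1, which is the severity heading). It lists factors to weigh but no rating categories. The AE definition in 9.3 mentions events related or not related to the product, but that is part of the definition of an AE and not a rating level.

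**Step 2: values that 11.5.2.6 counts as related**

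R = {unlikely, possible, probable, definite, missing}: 5 values.

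**Step 3: compare**

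R covers 5 of 5 values of V, and V minus R is empty. So 100% of TEAEs are classed as adverse drug reactions, whatever the investigators record and whichever group the patient is in.

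**Step 4: effect on the planned tables**

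| Related row in 11.5.2.6 | Must equal | Is that a listed overview row? |
|---|---|---|
| Related severe TEAEs | Severe TEAEs | Yes |
| Related TEAEs leading to permanent discontinuation | TEAEs leading to permanent discontinuation | Yes |
| Related TEAEs leading to death | TEAEs leading to death | Yes |
| Related TEAEs | All TEAEs | No; the list has All AEs, which includes pre-treatment AEs |

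Three of the four related rows duplicate a listed row, so their between-group differences and 95% CIs are repeats. The fourth equals a total that the overview list does not show as a row. The SOC and preferred-term tables by relatedness have nothing in the unrelated part.

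**Step 5: consistency with 14.1.4**

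A reaction there needs evidence or argument suggesting causality, and 14.1.6.2 asks about a reasonable possibility. An event rated unlikely does not naturally meet either standard, yet 11.5.2.6 gives it the adverse-drug-reaction label.

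**Step 6: after a correction**

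- Take unlikely out of R: 4 of 5 values are related and 1 of 5 is not. The split works.
- Or keep R and add a not-related level to V: 5 of 6 are related and 1 of 6 is not. The split also works.

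These are counts of rating levels, not of events. The documents do not allow an estimate of how many events would move.

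**The case against.** The strongest reply is that counting unlikely and missing as related is a conservative tabulation convention, separate from the pharmacovigilance definition in 14.1.4, and that the real slip is only the lack of a level below unlikely. Section 9.3.1.2 opens with a general qualifier, and the plan for tables by relatedness suggests the authors assumed an unrelated level existed; the eCRF, which is not shown, may contain one. Part of this stands. Counting missing as related is normal and is not criticised here, and counting unlikely as related would be workable if a lower level existed. But 9.3.1.3 repeats the four levels, without the qualifier, for the variable actually collected. The protocol as written therefore leaves no route to an unrelated TEAE.

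It is also fair that little safety inference rests on attribution in a placebo-controlled trial. The key safety endpoints in 11.5.2.5 and the all-causality AE rows are compared between randomised groups whatever the rating. This stands, and it limits the severity.

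Three stronger readings are tempting, and the documents do not support them:

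- **That all four related rows duplicate other overview rows.** Only three do, because no row for all TEAEs is listed.
- **That the IDMC and the report lose the causality information.** Section 11.5.2.6 also requires AE listings that show the relationship to study medication, so the raw grading is kept. What is lost is the summary split.
- **That SUSAR reporting is compromised.** All SAEs are reported regardless of causality (9.3.3), and reaction and SUSAR status are defined in 14.1.4 and 14.1.5 without reference to the rule in 11.5.2.6. A link to expedited reporting would be inference.

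**Conclusion.** The point holds. Under the protocol as written, every TEAE in both groups is analysed as an adverse drug reaction: 5 of 5 possible rating states are related. Three overview rows repeat their all-causality counterparts, the Related TEAEs row equals the total of all TEAEs, and the unrelated part of the planned tables is empty. The rule also conflicts with the protocol's own definition of an adverse reaction.

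This is a stated rule that gives a wrong result, not a detail left to the SAP. It affects descriptive safety tables only. The primary endpoint, the key safety endpoints and the all-causality AE comparisons do not depend on it. The conclusion assumes that the eCRF carries the four levels in 9.3.1.3 and that no SAP has already replaced the rule. Severity: should be fixed.

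**What to change.** In 11.5.2.6, define a TEAE as related if it is rated possible, probable or definite, or if the rating is missing; unlikely then counts as not related. This alone restores the split, brings the rule closer to 14.1.4, and needs no eCRF change and no recoding of existing records.

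Preferably, also add a not-related level to the scale in 9.3.1.2 and 9.3.1.3. AEs are collected from consent (9.3.2), so some occur before any study drug is given, and today the lowest rating available for them is unlikely. With the redefined rule, unlikely and not related fall on the same side, so ratings already entered can stay. Adding the level while keeping the present rule would also create a split, but unlikely ratings entered before the change would still be analysed as related.

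The cost is a small amendment: one sentence for the rule and, if the level is added, one more code-list value. A protocol amendment needs ethics and regulatory approval (12.1). Section 11.1.3 also provides for known departures from the planned analyses to be described in the final SAP before data collection is complete. In either case the change should be made before database lock.

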#### 11.5.2.7 SAFETY LABORATORY DATA

Laboratory data will be summarized by type of laboratory test after all results are converted to standard SI units. Descriptive statistics will be calculated for each laboratory parameter at baseline

and at each scheduled time point. Shift tables using the categories 'lower than normal range', 'within normal range' and 'higher than normal range' will be provided for each parameter, comparing the baseline value to all post-baseline values.

Listings of each laboratory parameter will be provided, marking changes from norm. A separate listing will be produced for clinically significant abnormal results.

#### 11.5.2.8 OTHER SAFETY DATA

Vital signs summaries will take form of tables presenting descriptive statistics for BP and HR as well as shift tables of result categories presenting changes when compared to baseline (Screening visit). Listings flagging abnormal values will be also produced.

ECG variables that will be analysed include heart rate, QTc intervals and ECG findings. In case of heart rate values  $\leq 50$  bpm will be classified as abnormal low, while values  $\geq 100$  will be classified as abnormal high.

ECG summaries will take form of tables for raw data and changes from baseline (values collected during screening) as well as percentage of abnormal values. In addition, shift tables presenting number of patients that either developed abnormalities in heart rate or QTc (or had such abnormalities subsume) since baseline will be provided.

The number of patients with at least one clinically relevant finding detected during the physical examination or the ECG will be summarized in frequency tables for each scheduled assessment or visit.

### 11.5.3 OTHER ANALYSES

#### 11.5.3.1 EXPLORATORY ANALYSES

Exploratory analyses will be described in an appropriate SAP before the analyses take place.

#### 11.5.3.2 SUB-GROUPS ANALYSES

All subgroup analyses will be descriptive in nature. It will include primary, secondary and exploratory endpoints analyses.

Detailed definition of subgroups will be provided in SAP.

### 11.5.4 PLANNED INTERIM ANALYSES

Primary endpoint analysis for each study arm (dabigatran, apixaban, or rivaroxaban) will be performed independently. Proportion of subjects achieving primary endpoint for active treatment and placebo as well as difference of proportions together with 82% Confidence Interval (CI) will be calculated. One-sided noninferiority test with 15% margin for difference in proportions will be performed. A p value lower than 0.176 will be considered as statistically significant.

#### 11.5.4.1 INTERIM ANALYSIS OF EFFICACY AND SAFETY ENDPOINTS

An interim analysis is planned after half of the randomized subjects reach primary endpoint (functional status assessment with modified Rankin scale on day 90). All collected data will be analysed. Primary endpoint will be tested using one sided  $\alpha=0.0238$ .

#### 11.5.4.2 PLANNED INTERIM ANALYSIS OF EARLY SAFETY DATA

Analysis will cover safety endpoints. For this purpose, data listings of adverse events, vital signs, adverse events, physical examinations, ECG and echocardiography will be prepared.

---

#### 11.5.4.3 INDEPENDENT DATA MONITORING COMMITTEE (IDMC)

An IDMC (see Section 10.3.3) will be established to reassure participants overall safety and to monitor the progress of the clinical study at regular intervals. This will include reviewing unblinded safety and tolerability data and the efficacy data from the Interim Analysis.

## 12 SUPPORTING DOCUMENTATION AND OPERATIONAL CONSIDERATIONS

### 12.1 REGULATORY, ETHICAL, AND STUDY OVERSIGHT CONSIDERATIONS

This study will be conducted in accordance with the protocol and with the following:

- Consensus ethical principles derived from local and international guidelines including the Declaration of Helsinki
- Applicable ICH GCP Guidelines
- Applicable laws and regulations

The study protocol, protocol amendments, ICF, IB, and other relevant documents will be submitted to an IRB/IEC by the investigator for review and approval by the IRB/EC before the study is initiated.

Any amendments to the study protocol will require IRB/IEC and applicable Regulatory Authority approval before implementation of changes made to the study design, except for changes necessary to eliminate an immediate hazard to study participants.

50Bio CRO (on behalf of the Sponsor) will be responsible for obtaining the required authorisations to conduct the study from the concerned Regulatory Authority.

#### 12.1.1 CASE REPORT FORMS (CRFS)

Study data will be collected via web-based electronic Case Report Form (eCRF).

BioStat Ltd. will be responsible for eCRF design, maintenance and oversight of the database created based on information entered in the eCRF

#### 12.1.2 TRIAL DATA AND DOCUMENTATION HELD AT SITES

Study records and documents, including signed ICFs, related to the conduct of the STROACT study must be retained by the investigator according to local regulations or institutional policies. No records may be destroyed during the retention period without the written notification of the Sponsor.

#### 12.1.3 STUDY DISCONTINUATION AND CLOSURE

The study may be terminated before the planned end of study by the principal investigator's decision if it is found that the patients participating in the study are exposed to unnecessary health risks. Such decision should be based on IDMC recommendations and the well-being of patients will always be put first in the considerations before decision about premature study termination is taken.

#### 12.1.4 CONFIDENTIALITY AND PRIVACY

All personnel involved in the STROACT study must comply with applicable data protection laws and regulations. To anonymize patient's data collected during the study standard procedures will be applied.

- Participants will be assigned a unique identifier by each study centre (screening number specific for the patient and study centre) and also randomisation number (specific number in the study to allocate study treatment) which will be generated in the eCRF system (see Section 6.2 and Section 6.4). Any participant records or datasets that are transferred to the sponsor will contain the identifier only; participant names or any information which would make the participant identifiable will not be shared (transferred).

- The participant will be informed that his/her personal study-related data will be used by the Sponsor in accordance with local data protection law. The level of disclosure and use of their data will also be explained to the participant in the informed consent.

---

#### 12.1.5 FUTURE USE OF STORED SPECIMENS AND DATA

There is no plan to collect specimens for future evaluation or analyses.

Clinical data obtained during the study can be used for future analyses, if deemed appropriate by participating Investigators.

---

#### 12.1.6 KEY ROLES AND STUDY GOVERNANCE

The EC (see [Section 10.3.1](#)) will provide operational management of the STROACT study including protocol design and general oversight of the study conduct. Specific responsibilities will be delegated to CROs as appropriate.

The SC (see [Section 10.3.2](#)) will be responsible for implementation and oversight of study procedures at the study centre level, monitor progress in enrolment, and contribute to the ongoing analysis and interpretation of incoming clinical efficacy and safety data for individual patients.

---

#### 12.1.7 SAFETY OVERSIGHT

The investigator and any designees at each study centre are responsible for patient safety during participation in the STROACT study.

To reassure adequate safety oversight at the study level the IDMC will be established (see [Section 10.3.3](#)).

Individual safety information will be monitored on the ongoing basis and accumulated data will be reviewed periodically. Specification of key safety data, frequency and format will be described in Safety Management Plan (SMP) and SAP.

---

#### 12.1.8 CLINICAL MONITORING

50Bio (CRO) will be responsible for clinical monitoring during the study duration and will follow own applicable SOPs, unless agreed otherwise with the Sponsor.

---

#### 12.1.9 PROTOCOL DEVIATIONS AND VIOLATIONS

For purposes of the STROACT clinical trial, a **protocol deviation (PD)** is defined as a departure from the approved **protocol's** procedures made with or without prior EC/IRB approval. Such departures may be major or minor/administrative in nature.

**Protocol violation (PV)** is defined as an important **protocol deviation** which may have potential impact on safety of the research participant or scientific integrity of the study

Study will be monitored for occurrence of PDs/PVs on the ongoing basis and identified cases will be assessed and reported according to the local competent authorities and appropriate EC/IRB requirements.

Identified PDs/PVs will be also reported in the Clinical Study Report.

Prospective approval of protocol deviations to recruitment and enrolment criteria, also known as protocol waivers or exemptions, is not permitted.

#### 12.1.10 STUDY RECORDS RETENTION

Each site / Principal Investigator is responsible for study records retention. Records and documents, including signed ICFs, pertaining to the conduct of this study must be retained by the investigator in accordance with local regulations after study completion unless local regulations or institutional policies require a longer retention period.

#### 12.1.11 FINANCING AND INSURANCE

The STROACT project is supported by the grant from the Medical Research Agency based on a proposal from the Medical University of Gdańsk No: 2019/ABM/01/00084.

The sponsor is responsible for the possession of the OC insurance for damage caused in connection with the conduct of the clinical trial, in accordance with the rules laid down in the Regulation of the Minister of Finance of 30 April 2004 on compulsory insurance against civil liability of the investigator and sponsor.

#### 12.1.12 PUBLICATION AND DATA SHARING POLICY

The results of the STROACT study are intended to be published and/or presented at scientific meetings. The EC will be responsible for study data analysis, presenting and publishing (see also [Section 10.3.1](#))

### 12.2 ABBREVIATIONS

| Abbreviation | Description                                    |
|--------------|------------------------------------------------|
| ADL          | Activities of Daily Living                     |
| AE           | Adverse Events                                 |
| AF           | Atrial Fibrillation                            |
| aICH         | Asymptomatic Intracranial Haemorrhage          |
| AIS          | Acute Ischaemic Stroke                         |
| AHA          | American Heart Association                     |
| ALAT         | Alanine aminotransferase                       |
| aPTT         | Activated partial thromboplastin time          |
| ASA          | American Stroke Association                    |
| ASPECTS      | Alberta Stroke Program Early CT Score          |
| BI           | Barthel Index                                  |
| BNP          | Brain natriuretic peptide                      |
| BP           | Blood Pressure                                 |
| CBC          | Complete Blood Count                           |
| CRP          | C-reactive protein                             |
| CSR          | Clinical Study Report                          |
| CT           | Computed Tomography                            |
| CTA          | CT angiography                                 |
| CTCAE        | Common Terminology Criteria for Adverse Events |
| CTP          | Clinical Trial Protocol                        |
| DBP          | Diastolic blood pressure                       |
| EC           | Executive Committee                            |
| eCRF         | Electronic Case Report Form                    |
| eGFR         | Estimated Glomerular Filtration Rate           |
| ECASS        | European Cooperative Acute Stroke Study        |
| ECG          | Electrocardiogram                              |
| EOS          | End of Study                                   |
| ESO          | European Stroke Organisation                   |
| HADS         | Hospital Anxiety and Depression Scale          |
| HR           | Heart Rate                                     |

|           |                                                                                |
|-----------|--------------------------------------------------------------------------------|
| IB        | Investigator's Brochure                                                        |
| ICF       | Informed Consent Form                                                          |
| ICH       | Intracranial Haemorrhage                                                       |
| IDMC      | Independent Data Monitoring Committee                                          |
| INR       | International normalised ratio                                                 |
| IS        | Ischaemic stroke                                                               |
| IQCODE    | Informant Questionnaire on Cognitive Decline in the Elderly                    |
| IVT       | Intravenous Thrombolysis                                                       |
| LPI       | Lead Principal Investigator                                                    |
| LVO       | Large Vessel Occlusion                                                         |
| MoCA      | Montreal Cognitive Assessment                                                  |
| MRA       | MRI angiography                                                                |
| MRI       | Magnetic resonance imaging                                                     |
| mRS       | Modified Rankin Scale                                                          |
| MT        | Mechanical thrombectomy                                                        |
| NIHSS     | National Institute of Health Stroke Scale                                      |
| MRI       | Magnetic Resonance Imaging                                                     |
| NOAC      | Non-Vitamin K Antagonist Oral Anticoagulant                                    |
| OAC       | Oral Anticoagulant                                                             |
| PI        | Principal Investigator                                                         |
| rtPA      | Recombinant tissue plasminogen activator                                       |
| SAE       | Serious Adverse Event                                                          |
| SAP       | Statistical Analysis Plan                                                      |
| SBP       | Systolic blood pressure                                                        |
| SC        | Steering Committee                                                             |
| sICH      | Symptomatic Intracranial Haemorrhage                                           |
| SITS-MOST | Safe Implementation of Thrombolysis in Stroke-Monitoring Study                 |
| SmPC      | Summary of Product Characteristics                                             |
| SoA       | Schedule of Assessments                                                        |
| SOC       | System Organ Class                                                             |
| SUSAR     | Suspected Unexpected Serious Drug Reaction                                     |
| STROACT   | ST Roke on O ral A ntiCoagulants for T hrombolysis |
| TFPI      | Tissue Factor Pathway Inhibitor                                                |

